### Participant recruitment

Participants will be identified as potentially eligible for inclusion in VAPOR 1 by their direct care teams at participating NHS hospital sites and diabetes education centres across England, Scotland and Wales. PDAC participants will be identified through HepatoPancreaticoBiliary multidisciplinary team meetings in addition to operating theatre, endoscopy, imaging or outpatient clinic lists, or emergency presentations to the hospital. Patients with new-onset diabetes mellitus will be identified by direct care teams, including diabetes specialist nurses and referrals from general practice. Those with chronic pancreatitis will be identified from hospital outpatient clinic, imaging or endoscopy lists and will be confirmed by imaging within no strict timeframe. Healthy controls will be identified through review of operating theatre, endoscopy, imaging and outpatient clinic lists, ensuring potential participants have undergone imaging confirming a normal pancreas within the last year. Patients in other research studies are eligible if requisite consent is given and the study has ethical approval. Potential participants will be approached about study participation by a member of their local VAPOR 1 research team. If they are interested in participating, they will be provided with the participant information sheet for the study. Where possible, participants will be given at least 24 hours to decide whether or not to take part in this study. In all instances, participants will be given the maximum time available to decide whether to take part in this study. Participant recruitment visits will be aligned with planned hospital appointments, investigations or procedures wherever possible. Fully informed written consent will be obtained prior to obtaining their breath sample, which is collected as two breath samples given at one time point.

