### Breath collection

All research team members who will be recruiting participants are trained in breath collection by an approved member of the Imperial College London VOC Laboratory. Participants are asked to fast, apart from water, for a minimum of 6 hours prior to breath collection. For participants undergoing surgery or a procedure, breath samples must be obtained preoperatively, prior to administration of sedation, anaesthetic or other pharmacological agents. After providing written informed consent, the research team will collect demographics, tumour characteristics and medical history from the participant (see online supplemental table 1). They will then be asked to rinse their mouth with water and provide breath samples by exhaling into two single-use breath collection bags via a mouthpiece that is subsequently sealed. A bespoke pump developed in-house will collect breath from each bag onto two thermal desorption (TD) tubes for 4 min, at a rate of 200 mL/min,^12^ resulting in four TD tubes per patient, each containing 800 mL of breath. Room air samples will also be collected onto two additional TD tubes to control for potential background environmental contamination. All TD tubes are transported at room temperature to the Imperial College London VOC Laboratory. Other factors that could affect VOC profiles, such as dietary intake and environmental exposures, including smoking, have been considered in the study design. As a result, participants are requested to fast for 6 hours prior to breath collection, with the time the participant last ate and drank recorded as well as the last cigarette and alcohol intake, if any. Figure 1 shows the study procedures before, during and after recruitment.

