#### Developing and reporting the CPM

Initially, relationships between candidate VOCs and the presence of PDAC will be explored using univariate logistic regression models, including linear, polynomial and cubic splines.

Given the large number of initial variables, a screening step will be undertaken to identify the most promising candidate VOCs for inclusion in statistical models, with approximately the top 50 being retained. To develop the CPM, a logistic regression model with variable selection and importance assessment techniques will be fitted. Robust variable selection methods will be used, specifically the least absolute shrinkage and selection operator (LASSO) and elastic net. LASSO aids in selecting a more parsimonious model by shrinking less important predictor coefficients to zero, while elastic net combines the penalties of LASSO and Ridge regression, effectively managing correlated predictors.^14^

Elastic net is particularly beneficial when dealing with highly correlated variables, as it can select groups of related predictors, making it well-suited for multivariate datasets like VOC profiles. The best-performing model, determined through nested cross-validation (CV), will be advanced for further analysis.

In addition to the statistical methods, random forest and deep neural networks (DNNs) will be used to enhance model predictions. Random forest constructs multiple decision trees from different data subsets and combines their predictions, handling complex, non-linear relationships in the VOC data and identifying key VOCs that predict PDAC. DNNs, capable of capturing patterns in high-dimensional data, will be employed to model non-linear relationships in the VOC data. The DNN architecture will include a designed number of hidden layers and neurons, with regularisation techniques like dropout applied to prevent overfitting.

The model will be enhanced by assessing the additional diagnostic value of patient and clinical features (eg, family history of cancer, presenting symptoms), potentially improving its predictive power and clinical applicability.

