A 10-fold CV will be used for internal validation of statistical and machine learning models. Nested CV will be applied to best identify the penalty terms in LASSO and elastic net models, as well as to fine-tune the hyperparameters in random forest and DNNs, reducing the risk of overfitting across all models. For each fold in the internal CV, the sensitivity, AUC, precision-recall AUC and the MAPE will be calculated and summarised by median (IQR) values across folds. Apparent performance with 95% CIs and optimism will be calculated by 100 bootstrap resamples. Predictors chosen in ≥50% bootstrapped selection routines will be taken forward.

For the final model, bias-corrected ROC (receiver operating characteristic) curves and calibration plots will be provided. All model coefficients with SEs, and ORs with 95% CIs will be reported.

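### Internal validation cannot separate PDAC signal from site, age or selection signal, and presenting symptoms are a candidate predictor although no study group is defined by symptoms

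*Protocol article*

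**What the plan says.** **Recruitment.** Under Participant recruitment, potential participants are identified "by their direct care teams at participating NHS hospital sites and diabetes education centres across England, Scotland and Wales". The routes then differ by group. For cases: "PDAC participants will be identified through HepatoPancreaticoBiliary multidisciplinary team meetings in addition to operating theatre, endoscopy, imaging or outpatient clinic lists", as well as emergency presentations. For one part of the benign group: "Patients with new-onset diabetes mellitus will be identified by direct care teams, including diabetes specialist nurses and referrals from general practice". Chronic pancreatitis and healthy controls come from hospital lists, largely of the same kinds as those used for cases.

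**Comparability.** Definitions of study groups and Eligibility set an age floor of 18. They state no matching on age, sex, site or symptoms, and no group is defined by having symptoms.

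**Validation.** Under Developing and reporting the CPM: "A 10-fold CV will be used for internal validation of statistical and machine learning models". Tuning is nested, and "Apparent performance with 95% CIs and optimism will be calculated by 100 bootstrap resamples". Site is not mentioned.

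**Clinical features.** The same section enhances the VOC model by "assessing the additional diagnostic value of patient and clinical features (eg, family history of cancer, presenting symptoms". Derivation of diagnostic rules then takes referral, review and discharge thresholds from the final CPM. It compares net benefit with a policy of referring every symptomatic patient.

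**Safeguard for site air.** Breath collection says: "Room air samples will also be collected onto two additional TD tubes to control for potential background environmental contamination". The article does not say how these samples enter the model.

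**The concern.** Nested tuning and bootstrap optimism answer one question: how much performance is lost on new people drawn from the same mixture of sites, ages and routes. They do not show whether the model has learned the disease or something that goes with being a case in this sample. If case share differs between sites and breath carries a trace of the site, that trace helps prediction in training and test folds alike. The same holds for an age difference between groups that VOCs partly reflect.

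The clinical-feature step does not resolve this, because it measures what clinical features add to VOCs. A GP already knows the patient's age and sex, so the useful question is what breath adds to those.

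Presenting symptoms raise a different problem. The test is meant for symptomatic patients, but a healthy control needs only a normal pancreas on imaging. If cases report symptoms more often than controls, part of any gain from symptoms reflects how controls were chosen. That part would not transfer to a population in which everyone has symptoms, yet it could pass into the thresholds and the net benefit.

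**Working it through.** **Inputs from the article (Sample size).** 205 cases and two control groups of the same size, so 410 controls and 615 in total; planning AUC 0.86. The group sizes reproduce, taking a two-sided 5% level (not stated):

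- p(1−p)(z₀.₉₇₅+z₀.₈₀)²/d² = 0.85 × 0.15 × (1.960+0.842)²/0.07² = 204.2, so 205.
- 205/0.8 = 256.25, so 257 per group, and 3 × 257 = 771.

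Nothing below changes the sample size.

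**Inputs that are assumptions.** The article gives no number of sites, case mix by site, age distribution or symptom prevalence. Each figure below is therefore conditional.

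**Step 1: site signal under random folds.** Data were simulated for 205 cases and 410 controls at 20 sites, with 50 VOCs and no disease signal, so the true AUC is 0.50. The model was ridge logistic regression, with 40 runs per setting. Both fold schemes were scored the same way, by the median AUC across folds. Site share of VOC variance was set at 5%, 10% and 20%.

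| Case mix | Random 10-fold | Folds held out by site |
|---|---|---|
| Same at every site | 0.50 / 0.50 / 0.51 | 0.50 / 0.50 / 0.51 |
| 102 controls from five case-free centres, even elsewhere | 0.52 / 0.53 / 0.55 | 0.51 / 0.49 / 0.50 |
| Case share varying by site | 0.55 / 0.58 / 0.63 | 0.51 / 0.50 / 0.51 |

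The equal-mix runs themselves range from 0.50 to 0.51, so differences of 0.01 should not be read. The excess over 0.50 is about 0.02 to 0.13 where case mix is uneven and absent where it is even.

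A second simulation used 20 centres, four of them control-only and supplying 100 controls, with case share varying elsewhere. Between-centre SD was 0.2, 0.3 or 0.5 of the within-centre SD. Random 10-fold AUC was 0.53, 0.57 and 0.62. Its leave-centre-out figure of 0.50 to 0.51 was computed within centres, so that contrast changes the AUC definition as well as the folds. The table above does not.

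**Step 2: what nuisance information could yield by itself.**

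- Knowing only that a participant came from a case-free centre: AUC = (1+f)/2, where f is the share of controls from such centres. For f = 10%, 25%, 50% this is 0.55, 0.625, 0.75. In the second row of the table f = 102/410 = 0.25, so the ceiling is about 0.62 and the simulated VOCs recovered 0.52 to 0.55.
- Age alone, with mean gap Δ and SD 12 years: AUC = Φ(Δ/(12√2)). For Δ = 5, 10, 15 this is 0.62, 0.72, 0.81. VOCs would carry age only in part, so this too is a ceiling.
- Symptoms alone, as a yes/no item with prevalence a in cases and b in controls: AUC = 0.5 + (a−b)/2. For 90% v 50% this is 0.70; for 90% v 30% it is 0.80.

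**Step 3: which problem each analysis can show.** Folds held out by site removed the site excess in every setting of the table. No fold scheme removes an age or symptom difference between groups, because it is present at every site. Those need a base model for comparison and a result without symptoms.

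**The case against.** The strongest reply is that much of this rests on silence in a condensed article. Fold construction and the use of room air may be set out in an analysis plan that is not shown, and grouped folds are not excluded. That stands, so no fault is asserted in how folds are built. What the article does state is the direction of the clinical-feature comparison and presenting symptoms as a candidate.

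Several stronger readings are tempting and are not supported:

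- *Cases and controls come from different centres.* The text supports this, at most, for diabetes education centres. How many controls they supply, and whether they see any PDAC, is not given. The other controls come from hospital lists.
- *Laboratory batches follow site.* All tubes go to one laboratory, with internal standards and quality-control samples, and nothing links batch to site.
- *Site air is ignored.* Room air is collected for this purpose; only its place in the model is unstated. The simulations include no background correction, so an effective one would shrink their figures.
- *Cross-validation causes the age and symptom problem.* It does not. Those are effects of selection that this validation cannot reveal.
- *Cases are symptomatic and controls are not.* Symptom status is fixed for no group; PDAC may be found incidentally, and controls from endoscopy or imaging lists may have symptoms.
- *Diabetes or pancreatitis status is a predictor.* The article does not name either as one.

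The article also lists the gap between secondary-care recruitment and primary-care use as a limitation, includes the diabetes cohort to reduce confounding, and aims only at internal validation. This disclosure is fair, but it does not tell a reader whether a good AUC reflects PDAC.

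**Conclusion.** The point holds as a worthwhile, inexpensive improvement. The stated validation deals with overfitting but cannot show whether performance comes from PDAC or from site, age or selection. If case mix varies by site, AUC can exceed 0.50 with no disease signal, by about 0.02 to 0.13 under the assumed site variation. If case mix is equal, there is no excess. Separately, the stated comparison does not show what breath adds to age and sex, and any gain from symptoms may partly reflect control selection and carry into the decision thresholds.

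A reader might infer that the eventual AUC will be inflated by a known amount, that 10-fold CV is wrong as the main validation, or that symptoms must be barred. None of these follows. The size of the bias cannot be derived from the article, and either change would be a trade-off that the point does not require.

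**What to change.** Keep the 10-fold CV and add the following to the analysis plan:

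1. Centre-held-out (internal-external) CV, with small centres pooled, scoring both schemes with the same AUC definition so that any gap is due to the folds.
2. The same modelling pipeline run on the room-air tubes as a negative control. An AUC clearly above 0.5 there would show that site air carries group information. State also how room air enters the breath model.
3. A base model with age, sex and smoking, and the VOC increment over it, as well as the planned increment of clinical features over VOCs.
4. The CPM and its net benefit reported without presenting symptoms, with the version including symptoms labelled exploratory.

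This is analysis work on data the study already plans to collect; recruitment and sample size do not change. The costs are extra analysis and noisier centre-held-out estimates. Centres that supply only controls would contribute nothing to an AUC computed within centres.

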### Sample size

The sample size of 205 PDAC cases was based on a target sensitivity of 85%, with 7% precision and 80% power, informed by pilot data on 132 patients.^10^ We aim to recruit the same number of each type of control, totalling 615 participants with complete data. Allowing for 20% attrition due to loss of samples, we will recruit 771 participants, which includes at least 256 with cancer.

Riley *et al*^11^ also recommend ensuring that the sample size achieves small mean absolute prediction error (MAPE), defined as the mean absolute difference between predicted and observed outcomes (cancer=1, no cancer=0), and large variation explained by the CPM, measured by Cox-Snell R^2^, which ranges from 0 for no predictive value to 1 for perfect prediction. Additionally, the area under the receiver-operating curve (AUC) provides an estimate of the ability of the CPM to discriminate between cancer and non-cancer cases. The resulting CPM based on 615 participants will have an MAPE of 0.048, estimate cancer incidence with precision 0.088, and achieve a minimum Cox-Snell R^2^ of 0.431 based on forty predictors. The SE in the AUC achieved by the CPM will be 0.016, based on an AUC of 0.86.

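### The study is sized on sensitivity, but no stated output gives a confidence interval for validated sensitivity: cross-validation yields a median (IQR) over folds of 20–21 cases, and the 95% CI is tied to apparent performance

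*Protocol article*

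**What the plan says.** In the Protocol article, the Sample size section rests the number of cases on one quantity: "The sample size of 205 PDAC cases was based on a target sensitivity of 85%, with 7% precision and 80% power". With two control groups of the same size this makes 205 cases and 410 controls ("We aim to recruit the same number of each type of control, totalling 615 participants with complete data"). The section states no significance level, sidedness or reference value.

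The section Developing and reporting the CPM sets 10-fold cross-validation as the internal validation and fixes the summary: for each fold, "the sensitivity, AUC, precision-recall AUC and the MAPE will be calculated and summarised by median (IQR) values across folds". It continues: "Apparent performance with 95% CIs and optimism will be calculated by 100 bootstrap resamples". For the final model it promises bias-corrected ROC curves and calibration plots. Specificity is not in the list of fold metrics.

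The section Derivation of diagnostic rules weighs missed cancers against false alarms through net benefit, decision curves and a cost-weighted threshold.

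**The concern.** A study sized so that sensitivity is known to within a stated margin should report validated sensitivity with an interval that can be held against that margin. Two measures of uncertainty are stated, and neither does this.

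- The IQR across folds describes how sensitivity varies among groups of about 20 cases. It is a description of spread, not a confidence interval for the model's sensitivity.
- The 95% confidence interval is placed on apparent performance. The pipeline screens candidates down to about 50 VOCs, applies LASSO and elastic net, and also fits random forests and deep neural networks. Apparent performance after that much selection is expected to be optimistic. The plan recognises this by estimating optimism, yet the interval stays with the uncorrected figure.

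A reader could take the fold IQR for the precision of the estimate, or take the interval around apparent performance as evidence of how the test performs in new patients. A sensitivity shown without the specificity obtained at the same cut-off is also hard to interpret for a triage test.

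**Working it through.** **Inputs.** From Sample size: 205 cases, 410 controls, sensitivity 0.85, margin 0.07, power 0.80. From Developing and reporting the CPM: 10 folds. Assumed because not stated: two-sided 5% (one-sided 2.5%), and a reference sensitivity of 0.85 − 0.07 = 0.78.

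**1. The plan's own figure.** Normal approximation with the variance taken at 0.85:

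n = (1.960 + 0.8416)² × 0.85 × 0.15 / 0.07² = 7.849 × 0.1275 / 0.0049 = 204.2, rounded up to 205.

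Power at n = 205: the standard error is √(0.1275/205) = 0.0249, and Φ(0.07/0.0249 − 1.96) = 80.1%.

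The 205 cases and 80% power therefore reproduce. This is a power calculation against an implied 78%. Read as a plain 95% half-width, 7 points would need 1.96² × 0.1275 / 0.0049 = 100 cases, and 205 cases give 1.96 × 0.0249 = 0.049, or 4.9 points.

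**2. One fold.** 205/10 = 20.5, so folds hold 20 or 21 cases. One case moves fold sensitivity by about 5 points (1/20 or 1/21). Its standard error at 0.85 is √(0.1275/20) = 8.0 points, or √(0.1275/21) = 7.8 points.

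**3. Median and IQR over ten folds.** Simulation of 100,000 sets of ten folds (five of 20 cases, five of 21), true sensitivity 0.85, folds treated as independent binomials:

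| Quantity | Result |
|---|---|
| Standard error of the fold median | 3.05 points |
| Standard error of the pooled proportion, √(0.1275/205) | 2.49 points |
| Cases giving the fold median's precision if pooled, 205 × (2.49/3.05)² | about 137 |
| Mean width of the IQR | 9.3 points |
| Runs in which the IQR contains 0.85 | about 84% |

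The IQR arises here from sampling alone, with no real difference between folds. It does narrow with more data, because ten folds become larger folds: with three times the cases the mean width falls to about 5.3 points. At no size does it have the meaning of a 95% interval.

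**4. What a matching output would look like.** If 174 of the 205 cases were correctly classified out of fold, sensitivity would be 84.9%, with an exact 95% interval of 79.2% to 89.5%. That interval can be read directly against the margin and the implied 78%. It treats the 205 out-of-fold classifications as independent.

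**The case against.** The strongest reply is that the pieces are nearly all there. Optimism is estimated, so a corrected point estimate follows by subtraction. Bias-corrected ROC curves show specificity at every sensitivity, and false positives enter the decision rule through net benefit. The plan never calls the IQR a confidence interval, nothing prevents pooling, and 3.05 and 2.49 points are both well inside 7. An article may also leave interval methods to a fuller plan.

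Much of this stands. A corrected point estimate is available, and the cost of specificity being off the fold list is modest. It would be wrong to say that the plan ignores false positives or that any low cut-off would satisfy it. What does not fall away is that the article chooses its summaries explicitly: the fold median with IQR, and an interval on apparent performance. That is a stated method for which a better one exists, not an omitted detail. Neither the ROC curve nor the net-benefit analysis, as described, pairs a specificity with the cross-validated sensitivity or gives either an interval.

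A reader might also infer that the 80% power is wrong, because an exact calculation can give 71.0% (at least 172 of 205, against 78% at one-sided 2.5%). The document does not support that. It states no reference value, significance level or exact test, and at one-sided 5% the exact power is 82.5% (at least 170 of 205). The stated figure follows from a standard formula.

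**Conclusion.** The concern holds as a mismatch between the sizing and the reporting. The study is sized on sensitivity, and no stated output gives an interval for cross-validated or optimism-corrected sensitivity. The fold median loses precision equivalent to about a third of the cases (137 of 205 effective), and its IQR of about 9 points is not a confidence interval. These sizes assume a true sensitivity of 85% and folds that behave as independent binomials. In real cross-validation the training sets overlap, so they are approximate.

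The absence of specificity from the fold metrics is a secondary point, softened by the planned ROC curves and net benefit. The sample size and power are not in error. The sizing sentence would merely be clearer with its significance level and its implied 78% stated, since precision alone would be 4.9 points. The change is worth making before analysis, but it does not threaten the design.

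**What to change.** 1. Pool the out-of-fold predictions over all 205 cases and 410 controls. Report sensitivity and specificity together, each with a 95% confidence interval (for example Wilson), at a cut-off chosen inside the training data by the approach already set out in Derivation of diagnostic rules.
2. Put the bootstrap 95% interval on optimism-corrected performance, repeating the whole pipeline (screening, selection, tuning) in each resample.
3. Keep the median (IQR) across folds as a supplementary description of stability.
4. In Sample size, state the significance level, its sidedness and the reference sensitivity behind the 205 cases, and note that the expected 95% half-width at 85% is about 4.9 points.

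This needs no new participants or data. The cost is wording, a little more analysis and computing, and a headline figure less favourable than apparent performance.

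### 100 bootstrap resamples are enough for mean optimism but few for percentile 95% limits and for a 50% inclusion vote, so borderline VOCs could enter or leave the model with the random seed (minor)

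*Protocol article*

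**What the plan says.** The bootstrap is described in two adjacent sentences of the protocol article, section Developing and reporting the CPM. The first fixes the count: "Apparent performance with 95% CIs and optimism will be calculated by 100 bootstrap resamples". The second sets the entry rule: "Predictors chosen in ≥50% bootstrapped selection routines will be taken forward". The second has no count of its own, and no other bootstrap count appears in the article. The type of bootstrap interval is not named.

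The vote applies to a candidate list that has already been screened, "with approximately the top 50 being retained", using penalised logistic regression, "specifically the least absolute shrinkage and selection operator (LASSO) and elastic net". Internal validation is also done by 10-fold cross-validation with nested tuning, summarised by medians and IQRs over folds. That part does not use the bootstrap.

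The Sample size section supplies the scale for the check: "The SE in the AUC achieved by the CPM will be 0.016, based on an AUC of 0.86".

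**The concern.** One number serves purposes with different needs. Mean optimism is an average over resamples and settles quickly. A percentile 95% limit is a tail quantile; with 100 resamples it rests on about the second or third most extreme value. A 50% vote turns a proportion into a yes/no decision, and a proportion out of 100 is least precise at 50%.

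The vote matters more than the interval. It decides which predictors go forward, and so which coefficients and odds ratios are reported and which model generates the probabilities behind the referral, review and discharge thresholds. The article expects VOC predictors to be correlated. Correlated predictors can stand in for one another from resample to resample, which makes intermediate inclusion frequencies plausible. For such predictors, a rerun on the same data with another seed could give a different list. That noise comes from the computation, not from the patients, and it is cheap to reduce.

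**Working it through.** **Inputs.** From the article: B = 100 resamples; cut-off 50%; AUC 0.86 with SE 0.016; target sensitivity 85%; 205 cases and 615 participants in all. Assumed: the vote uses the same B = 100; the interval is either percentile or normal type, both shown; B = 1000 is the comparison.

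**The plan's own figures.** No derivation is given for 100, so there is nothing to reproduce for that number. The 205 cases do reproduce, taking two-sided α = 0.05 (not stated): (1.96 + 0.84)² × 0.85 × 0.15 / 0.07² = 204.2 with unrounded normal quantiles, rounded up to 205. The Hanley–McNeil formula gives an AUC SE of 0.0176 for 205 cases and 410 controls, against the stated 0.016. I use the stated value; the other would raise the AUC errors below by a tenth.

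**1. Percentile limits.** The Monte Carlo SE of a 2.5% bootstrap quantile, in units of the SE of the statistic, is √(0.025 × 0.975 / B) / φ(1.96), with φ(1.96) = 0.0584.

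- B = 100: 0.01561 / 0.0584 = 0.267. On the AUC: 0.267 × 0.016 = 0.0043.
- B = 1000: 0.00494 / 0.0584 = 0.084. On the AUC: 0.084 × 0.016 = 0.0014.
- Sensitivity at B = 100: √(0.85 × 0.15 / 205) = 0.0249, times 0.267 = 0.0067.

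A simulation with normally distributed bootstrap values gave 0.0039 for the AUC limit at B = 100. The lower limit ran from about 0.822 to 0.837 over the central 95% of seeds, on an interval about 0.06 wide. By order-statistic theory, the real content of a nominal 95% percentile interval lies between 88.7% and 97.8% over the central 95% of seeds at B = 100, and between 93.6% and 96.3% at B = 1000.

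**2. Normal-type limits.** The relative error of a bootstrap SE is 1/√(2(B − 1)): 0.071 at B = 100 and 0.022 at B = 1000. On an AUC limit this is 1.96 × 0.016 × 0.071 = 0.0022, and 0.0007 at 1000.

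**3. Mean optimism.** Taking 0.016 as a generous SD, the Monte Carlo SE at B = 100 is 0.016 / √100 = 0.0016. That is adequate.

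**4. The vote.** The SE of an inclusion frequency at 50% is √(0.25 / 100) = 5 points, and √(0.25 / 1000) = 1.6 points at 1000. Exact binomial probability of reaching at least 50% of resamples:

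| True inclusion | Kept, B = 100 | Kept, B = 1000 |
|---|---|---|
| 40% | 2.7% | about 0 |
| 45% | 18.3% | 0.08% |
| 50% | 54.0% | 51.3% |
| 55% | 86.5% (dropped 13.5%) | 99.93% (dropped 0.07%) |
| 60% | 98.3% | about 100% |

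If a VOC is kept with probability s, two seeds disagree on it with probability 2s(1 − s). For the 45% VOC this falls from 30% to 0.2%. For a VOC at exactly 50% it stays at about 50% whatever the count.

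**5. How many VOCs are affected.** This depends on effect sizes and correlations that the article cannot supply. Two illustrative logistic-LASSO simulations with 205 cases and 410 controls, both under assumed effects, show the range:

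- 50 candidates: two seeds differ by 0.7 to 5.7 VOCs at B = 100, and by 0.02 to 2.6 at B = 1000.
- 300 VOCs assumed, screen repeated in each resample: 2.6 VOCs differ and 94% of seed pairs are not identical at B = 100; 0.8 and 60% at B = 1000.
- 300 VOCs assumed, screen run once on all data: 1.3 VOCs and 27% at B = 100; 0.6 and 24% at B = 1000.

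**The case against.** The strongest reply is that this changes little.

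- **The link to the vote is inferred.** The sentence with the count concerns apparent performance, its intervals and optimism; the vote sentence has none. A separate count could be in an analysis plan that is not shown. This stands, and the vote argument is conditional on it.
- **The interval type is not stated.** With normal-type limits the error is about 0.002. Even at 0.0043, the total uncertainty of a limit rises only from 0.016 to √(0.016² + 0.0043²) = 0.0166, or 3.5%. These are intervals for apparent performance, and the cross-validated results do not rest on them. This stands.
- **A fixed seed would make the run repeatable.** True, but a borderline choice would still be settled by the seed chosen.
- **More resamples do not cure unstable selection.** VOCs very near 50% stay undecided at any count, and sampling instability remains. If the screen is run once, a natural reading of the article, the share of non-identical seed pairs hardly moves (27% against 24%). This stands as a limit on the gain.

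A reader might infer that two analysts following the plan would publish different panels, or that the whole panel depends on the seed. The article does not support that. VOCs with true inclusion below about 35% or above about 65% are essentially fixed even at 100 resamples. Exchanging borderline VOCs has not been shown to alter AUC, sensitivity, calibration or net benefit.

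**Conclusion.** The point holds in limited form and is minor. One hundred resamples are adequate for mean optimism. They are low for percentile 95% limits and, if the same count serves the vote, low for a decision taken at 50%. The seed affects VOCs with inclusion of roughly 40–60%; how many there are depends on unknown effects and on whether the screen is repeated in each resample.

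Nothing in the article is contradictory or wrongly calculated here, and no conclusion of the study is shown to change. The case for acting is that the noise is avoidable at little cost.

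**What to change.** In Developing and reporting the CPM, use at least 1000 resamples for the 95% confidence intervals and for the inclusion vote of the penalised logistic models, and say explicitly that the vote uses that count. The 100 may stay for the mean optimism of the slow learners (random forest, deep neural networks) if computing time requires it.

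Keep the 50% rule as the definite entry rule, and report each predictor's inclusion frequency beside it so that readers can see which entries were close. The frequencies are for reporting only and should not create a third category between in and out.

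The cost is computing time for the penalised logistic models. No data, recruitment or design feature changes.
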